#### SBRT

SBRT will be planned within 4 weeks from chemotherapy completion. Fiducial markers will be placed via EUS prior to CT-simulation. SBRT will be delivered only at the Verona Pancreas Institute as follows: patients are immobilized in supine position with arms over the head, using a custom-made Vac-Lok™ cushion. Abdominal compressor or inspiration breath hold (IBH) technique are used to manage breathing induced tumor motion. To give respiratory feedback to the patient a Real-Time Position Management® system (Varian Medical Systems, Palo Alto, CA) will be used. The gross tumor volume (GTV) is delineated as the radiographically evident gross disease on a multi-phases contrast-enhanced simulation CT. An internal target volume (ITV) will be defined as the envelope of the GTVs from each CT-phase. An ITV to Planning Target Volume (PTV) margin of 5 mm is applied. For organs at risk such as duodenum, stomach and bowel, a 3 mm expansion planning organ at risk volume (PRV_oar_) is defined. In case of proximity of the target volume to organs at risk, a simultaneous protection volume (PTV_sip_) will be generated as the intersection of the PTV and the PRV_oar_. A simultaneous integrated boost (SIB) to the tumor vessel interface (TVI) is planned. SBRT plans will be delivered using RapidArc® technique (Varian Medical Systems, Palo Alto, CA, USA) by a True Beam® linear accelerator (Varian Medical Systems, Palo Alto, CA, USA) with a 6-MV flattening filter-free (FFF) photon beam energy to minimize treatment duration. The standard schedule involves delivery of 30 Gy in 5 consecutive daily fractions to the PTV, with a boost on the TVI up to 50 Gy (accepted range 40–50 Gy, corresponding to a biologically effective dose (BED_10_) of 72–100 Gy). The prescribed dose will be reduced to 25 Gy (5 Gy/fraction) on the PTV_sip_, in order to avoid toxicities. Normal tissue constraints are as follows: for duodenum, small bowel and stomach Dmax < 35 Gy, V30 Gy < 5 cc, Dmean < 20 Gy; for spinal cord Dmax < 20 Gy; for kidneys Dmean < 10 Gy and D200cc < 17,5 Gy; for liver D700cc < 21 Gy. On-line image guidance (IGRT) will be performed by means of cone beam computed tomography (CBCT) before every single treatment session.

Patients completing SBRT will be re-staged with thin-slice contrast-enhanced tri-phasic computed tomography to rule out distant progression and will be further re-evaluated at the Pancreas Institute Oncological multidisciplinary meeting.

#### Intraoperative determinants of resectability

All surgeries will be carried out at the Verona Pancreas Institute. Determinants of intraoperative resectability will be:
Absence of distant metastases,Absence of portal vein cavernoma (unreconstructible venous anatomy),No need for superior mesenteric artery resection.Acceptable arterial resections include common hepatic artery resection (performed only when a short segment – up to 2 cm – is involved), and Appleby or modified Appleby procedure (performed for solid tumor contact with celiac trunk, without aortic involvement) [21].

#### IORT

IORT will be delivered in a dedicated hybrid operating room with a portable linear accelerator (Mobetron®, IntraOp Medical Corporation, Sunnyvale, CA, USA) provided with a set of collimator (collimator diameter ranging from 3 to 10 cm (step 0.5 cm) each one with bevel angle of 0°, 15° or 30°). Following the resection phase, the radiation oncologist and the surgeon will decide the collimator dimension and the angle of bevel, according to post-surgical anatomy and tumor bed characteristics. For unresectable tumors, collimator dimension and bevel angle will be defined after surgical exploration according to tumor dimensions. Collimator dimension will be selected to encompass with a 1-cm margin the resection bed or in situ tumor. Guidelines for radiation dose are as follows: resection bed 10–15 Gy; unresectable tumor 13–20 Gy. In case of unresectable head/neck tumors a gastrojejunostomy will be performed (to avoid a possible gastric outlet obstruction due to bowel edema). A cholecystectomy may be performed if indicated.

### Postoperative management

Patients will be managed according to our standard practice. Procedure-specific complications, including pancreatic fistula, post-pancreatectomy hemorrhage, delayed gastric emptying, and chyle leak will be defined according to the International Study Group of Pancreatic Surgery recommendations [22–24]. Infectious, pulmonary, cardiac, neurologic, and renal complications will be also recorded. Postoperative complications will be graded according to the Clavien-Dindo classification [25]. Hospital readmission and 90-day postoperative mortality will be recorded.

### Follow-up

#### Efficacy assessment

Patients will be followed for 36 months postoperatively or from the time of early progression/surgical ineligibility. Follow-up visits will take place every 3 months after surgery for the first 12 months, then on a 6-month basis up to study completion/death (Table 1). In patients with disease progression during the neoadjuvant phase and in those who were not eligible for surgical exploration, follow-up visits will be scheduled on a 6-month basis. The surveillance protocol includes a thin-slice contrast-enhanced, tri-phasic computed tomography, Ca 19.9 measurement and a thorough clinical examination. Complementary gadolinium-enhanced magnetic resonance and/or 18-FDG positron-emission tomography will be performed in selected cases, following multidisciplinary consultation. Disease recurrence (either local or distant) is defined as the presence of biopsy-proven tumor or was assumed based on the above-mentioned cross-sectional imaging studies, in conjunction with clinical picture and/or serum Ca 19.9 levels.

**Table 1 Tab1:** Flow-chart of study procedures

	Pre-study	PC completion	SBRT completion	Surgery + IORT^**a**^	Follow-up							
Assessments												
Informed consent	X				3 mo	6 mo	9 mo	12 mo	18 mo	24 mo	30 mo	36 mo
Physical evaluation	X	X	X	X	X	X	X	X	X	X	X	X
AE assessment		X	X	X	X	X	X	X	X	X	X	X
Ca 19–9, CEA	X	X	X	X	X	X	X	X	X	X	X	X
CT-scan (thorax/abdomen)	X	X	X		X	X		X	X	X	X	X
MRI	Optional	Optional	Optional									

*PC* primary chemotherapy, *IORT* intraoperative radiation therapy

^a^at the time of hospital discharge

### Statistical considerations

#### Sample size calculation

The estimate of accrual was calculated hypothesizing that total neoadjuvant therapy with FOLFIRINOX + SBRT + IORT will improve the 3-year survival rate up to 37% in comparison with cohort-level institutional data (patients < 75 years with BRPC undergoing neoadjuvant FOLFIRINOX, 3-year survival of 23.7%) Accrual time was set at 36 months and follow-up at 36 months. At a power of 0.90, and alpha of 0.5 a sample size of 100 patients was calculated assuming a non-parametric estimate of survival distribution. The SWOG Cancer Research and Biostatistics one-arm trial with time-to-event data sample size calculator was employed [26].

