#### Survival analysis

The progression-free survival (for patients who will not ultimately receive pancreatectomy due to unexpected locally unresectable or metastatic disease) and the disease-specific survival (for patients receiving pancreatectomy) will be calculated from both the date of diagnosis and the date of last follow-up or recurrence/death from disease, using the Kaplan-Meier method. Pairwise differences in survival will be assessed using the log-rank test. The analysis of recurrence and survival predictors will be carried out using the proportional hazard Cox regression (backward stepwise elimination technique, Wald method, *P* < .05 for entry, *P* > .10 for removal). Statistical significance will be determined by a 2-sided *P* value less than .05. Data will be using SPSS software (IBM).

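### The sample size paragraph prints alpha 0.5, which cannot give 100 patients; correcting the digit still leaves the sidedness, and so the 90% power, to be reconciled with the 2-sided .05 rule

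*Protocol article*

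**What the plan says.** Protocol article, Sample size calculation: the regimen "will improve the 3-year survival rate up to 37"%, against institutional data with a "3-year survival of 23.7"%. "Accrual time was set at 36 months and follow-up at 36 months". The sizing sentence is "At a power of 0.90, and alpha of 0.5 a sample size of 100 patients was calculated", continued by "assuming a non-parametric estimate of survival distribution". A one-arm time-to-event calculator is cited. Neither the sidedness of alpha nor the scale or variance form used by the calculator is given.

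Protocol article, Survival analysis: after the Kaplan-Meier, log-rank and Cox methods, "Statistical significance will be determined by a 2-sided" P value below .05. This is the only significance rule in the document. It neither mentions the comparison with 23.7% nor exempts it, and no section declares a one-sided test.

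**The concern.** Alpha and power are the two error rates that justify a single-arm trial against a fixed historical rate. As printed, alpha is ten times the conventional 0.05 and does not fit the sample size beside it. The obvious repair is to read 0.05, but that does not close the matter. The figure of 100 fits a one-sided 0.05 calculation well, while the only stated decision rule is 2-sided. A reader who silently corrects the digit and applies the stated rule would credit the trial with 90% power that it may not have.

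The choice can also decide the result. With exactly 32 of 100 patients alive at 3 years, an exact test succeeds at one-sided 0.05 (tail probability 0.036) and fails at two-sided 0.05, which allows 0.025 in the upper tail.

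**Working it through.** **Inputs**, all from Sample size calculation: p0 = 0.237, p1 = 0.37, power 0.90 (z_b = 1.2816), n = 100, 36 months' accrual and 36 months' follow-up. Assumptions: follow-up runs from last accrual, so nobody is censored before 3 years, and there is no dropout (none is stated).

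**Formulas.** On a scale g, let d be the distance between g(p1) and g(p0), and let s0 and s1 be the per-patient standard deviations under the null and the alternative.

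- n = [(z_a·s0 + z_b·s1) / d]²
- power = Φ[(√n·d − z_a·s0) / s1]

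z_a is 1.6449 (one-sided 0.05), 1.9600 (two-sided 0.05), 0 (one-sided 0.5) or 0.6745 (two-sided 0.5).

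**Score form in full.** d = 0.133, s0 = √(0.237 × 0.763) = 0.4252, s1 = √(0.37 × 0.63) = 0.4828.

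- Alpha 0.5 one-sided: (0 + 0.6188)/0.133 = 4.652, squared 21.6.
- Alpha 0.5 two-sided: (0.2868 + 0.6188)/0.133 = 6.809, squared 46.4.
- Alpha 0.05 one-sided: (0.6994 + 0.6188)/0.133 = 9.911, squared 98.2. Power at 100 = Φ[(1.33 − 0.6994)/0.4828] = 0.904.
- Alpha 0.05 two-sided: (0.8334 + 0.6188)/0.133 = 10.919, squared 119.2. Power at 100 = Φ[(1.33 − 0.8334)/0.4828] = 0.848.

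**The forms that reproduce 100** (n before rounding up; log-log uses the Greenwood variance):

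| Form | n, 0.5 one-sided | n, 0.5 two-sided | n, 0.05 one-sided | Power at 100, 0.05 one-sided | n, 0.05 two-sided | Power at 100, 0.05 two-sided |
|---|---|---|---|---|---|---|
| Score | 21.6 | 46.4 | 98.2 | 0.904 | 119.2 | 0.848 |
| Arcsine | 19.4 | 45.2 | 101.2 | 0.897 | 124.2 | 0.829 |
| Log-log, null and alternative variance | 20.6 | 46.4 | 101.6 | 0.896 | 124.1 | 0.831 |
| Log-log, null variance | 18.6 | 43.4 | 97.1 | 0.908 | 119.1 | 0.844 |

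**Exact binomial at n = 100.** Two-sided 0.05 needs at least 33 survivors: upper-tail error 0.022, power 0.824. One-sided 0.05 needs at least 32: error 0.036, power 0.873. The 90% is therefore a normal-approximation figure even one-sided.

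**Other non-parametric forms** (identity, log-log, log and logit scales, with the remaining choices of variance):

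- Alpha 0.5: n runs from 14.1 (log scale, alternative variance) to 26.6 (log scale, null variance) one-sided, and from 32.8 to 62.1 two-sided. No form comes near 100.
- Two-sided 0.05 at n = 100: power runs from 0.699 (log scale, null variance) to 0.927 (log scale, alternative variance).

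**Parametric cross-check.** With exponential survival, the log hazard ratio is 0.3702 and the probability of an event over 36 + 36 months under the alternative is 0.7656. Two-sided 0.05 then needs (1.9600 + 1.2816)²/0.3702² = 76.7 events, and 76.7/0.7656 = 100.2 patients.

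**The case against.** The strongest reply is that 0.5 is plainly a dropped zero: the next subsection uses .05, and nothing suggests that anyone would act on 0.5. That is very likely true. A reader might take the printed value literally and infer that success would be declared at 25 of 100 survivors, with a false-positive rate of about 42%. The article gives no support for such an intention, so the value should be treated as a misprint of a key design figure, not as a design choice.

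A reader might also infer that 100 can come only from one-sided 0.05. The documents do not establish this. The calculator's scale and variance form are not shown, and several non-parametric forms miss 100 at one-sided 0.05. One of them (log scale, alternative variance) needs about 90 patients at two-sided 0.05 and gives 92.7% power with 100. The exponential calculation also lands on 100 at two-sided 0.05, although it contradicts the non-parametric assumption stated. One-sided 0.05 is the best fit, not a proven input. The 83-85% is conditional in the same way, because it comes from the forms that reproduce 100.

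Finally, the 2-sided rule follows the log-rank and Cox methods and does not say that it covers every analysis. If the primary test was meant to be one-sided, 90% power is approximately delivered and what remains is the misprint and an unclear scope. That stands. But the rule is the only one given, it sits under the heading that covers survival, and the primary endpoint is a survival rate, so its scope needs stating. A condensed article may leave out sidedness; the point here is that what it does print does not fit together.

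**Conclusion.** The printed alpha of 0.5 is wrong: no sidedness and no form tried turns it into 100 patients at 90% power. This holds without any assumption about the calculator's settings.

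The second part is conditional. If the sizing used one-sided 0.05, which fits best, and the 2-sided .05 rule governs the comparison with 23.7%, power at 100 patients is about 83-85%, a loss of some 5 to 7 percentage points from the stated 90%. The exact binomial figure is 82%, and the range is about 70-93% if the scale and variance form are left open. These figures assume complete follow-up to 3 years. A reader might infer that the trial is underpowered or needs more patients; the article does not support that, because the sponsor's actual inputs and the intended primary test are not shown.

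**What to change.** 1. Check the inputs entered in the calculator. In Sample size calculation, replace the alpha of 0.5 with the confirmed value and state whether it is one- or two-sided.
2. In Survival analysis, say which significance rule governs the primary comparison with 23.7%.
3. If the inputs were one-sided 0.05, declare the primary test one-sided at 0.05 before the analysis, and keep 2-sided .05 for the other analyses.
4. If 2-sided 0.05 is kept for the primary test, restate the power at 100 patients as about 83-85%, or as the value the confirmed calculator gives.

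The cost is one look at the calculator inputs and two sentences of wording. No extra patients are needed. Under option 4 the stated power would become less favourable, unless the confirmed calculator shows otherwise. The choice must be made before outcome data are seen, because choosing the sidedness afterwards would undermine the result.

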#### Survival analysis

The progression-free survival (for patients who will not ultimately receive pancreatectomy due to unexpected locally unresectable or metastatic disease) and the disease-specific survival (for patients receiving pancreatectomy) will be calculated from both the date of diagnosis and the date of last follow-up or recurrence/death from disease, using the Kaplan-Meier method. Pairwise differences in survival will be assessed using the log-rank test. The analysis of recurrence and survival predictors will be carried out using the proportional hazard Cox regression (backward stepwise elimination technique, Wald method, *P* < .05 for entry, *P* > .10 for removal). Statistical significance will be determined by a 2-sided *P* value less than .05. Data will be using SPSS software (IBM).

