## Methods/design

The study reporting adheres to the SPIRIT Guidelines [19]. This single-arm phase II trial will be conducted at the University of Verona Hospital Trust and will enroll newly diagnosed patients with BRPC. The trial has been registered at www.clinicaltrials.gov (NCT04090463) and has been approved by the local Ethics Committee (#2301CESC). The expected total study duration is 72 months (36 months for enrollment and 36 months for follow-up).

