### Endpoints

The primary endpoint is the 3-year disease-specific survival (intention-to-treat). Secondary endpoints include:
Completion of chemotherapy,Completion of SBRT,Acute and late toxicities,Resection rate,Perioperative morbidity and mortality,Rate of margin-free surgery,Progression-free survival (local/distant progression), intention-to-treat,Recurrence-free survival in the subset of patients undergoing resection (per-protocol),3-year disease-specific survival in the subset of patients undergoing resection (per-protocol).

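### The survival-analysis section gives disease-specific survival only for resected patients and PFS only for unresected ones, contradicting the intention-to-treat primary and PFS endpoints

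*Protocol article*

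**What the plan says.** **Endpoints section.** "The primary endpoint is the 3-year disease-specific survival (intention-to-treat"). The secondary list includes "Progression-free survival (local/distant progression), intention-to-treat" and, as a separate item, "3-year disease-specific survival in the subset of patients undergoing resection (per-protocol").

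**Chemotherapy and Restaging sections.** Patients who discontinue chemotherapy, and those not eligible for surgical exploration, stay in the intention-to-treat analysis. The Discussion calls this design the main strength of the study.

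**Methods/design and Sample size calculation.** "This single-arm phase II trial will be conducted" at one centre. The trial is sized to raise 3-year survival to 37% against an institutional "3-year survival of 23.7" per cent, with a one-arm time-to-event calculator and a non-parametric survival estimate. Power is 0.90, alpha is printed as 0.5, and N is 100.

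**Survival analysis section.** Two populations are named. One is "The progression-free survival (for patients who will not ultimately receive pancreatectomy due to unexpected locally unresectable or metastatic disease"); for the other, "the disease-specific survival (for patients receiving pancreatectomy) will be calculated". The group comparison is: "Pairwise differences in survival will be assessed using the log-rank test". Predictors go into a stepwise Cox model, and significance is set at 2-sided 0.05.

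**The concern.** The Survival analysis section divides the cohort by an outcome that occurs after enrolment, namely whether the patient is resected, and attaches a different endpoint to each part. The endpoint list requires both endpoints in everyone enrolled.

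Patients who stop for toxicity or declining performance status fit neither part, although the Chemotherapy section keeps them in the intention-to-treat analysis. The named test needs at least two groups, while the hypothesis concerns one group and a fixed value.

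At stake is which number answers the primary question. Resected patients are selected for not having progressed and for being fit for surgery. Their survival would exceed that of the whole cohort even if the new treatment did nothing, so it is no substitute for the intention-to-treat estimate.

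**Working it through.** **1. Populations side by side**

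| Endpoint | Endpoints section | Survival analysis section |
|---|---|---|
| Disease-specific survival, primary | all enrolled | not given |
| Disease-specific survival, resected | secondary, per-protocol | given |
| PFS | all enrolled | only patients not resected because of unexpected unresectable or metastatic disease |
| Comparison with 23.7% | basis of the sample size | none; pairwise log-rank and Cox only |

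**2. The plan's own figure, N = 100**

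Inputs from Sample size calculation: p0 = 0.237, p1 = 0.37, power 0.90 (z = 1.282). Follow-up to 36 months is taken as complete.

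- Normal approximation: n = [(z_a·√(p0·q0) + z_b·√(p1·q1)) / (p1 − p0)]². At one-sided 0.05 this is [(1.645 × 0.4252 + 1.282 × 0.4828) / 0.133]² = 98.2.
- Arcsine square root: n = [(1.645 + 1.282) / 0.2909]² = 101.2.
- Log(−log) scale: 101.6.

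So N = 100 reproduces (98-102) as a one-sample test in all enrolled patients at one-sided 0.05. At 2-sided 0.05 the same formulas give 119-124, and power at n = 100 is about 0.83-0.85. At the printed alpha of 0.5 they give 19-22 (one-sided) or 45-46 (two-sided). An exponential model at 2-sided 0.05 also gives 100.2, but the protocol states a non-parametric estimate.

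**3. What selection by resection does (illustration only)**

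Suppose whole-cohort 3-year survival is exactly 23.7%, so there is no treatment effect. Let r be the resection rate and s the 3-year survival of unresected patients. Then resected-only survival = (0.237 − (1 − r)·s) / r. The range s = 0 to 0.10 is an assumption. The values of r come from the Background:

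- 51%: patients under 75 given FOLFIRINOX in an observational study;
- 65%: the intention-to-treat margin-negative rate in a phase 2 trial, used as a proxy for the resection rate;
- 88.9%: the institution's own series after chemotherapy and SBRT.

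Example at r = 0.51: s = 0 gives 0.237/0.51 = 0.465; s = 0.10 gives (0.237 − 0.049)/0.51 = 0.369.

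Next, test n = 100r patients against 0.237 at one-sided 0.05. The rejection limit is 0.237 + 1.645·√(0.237 × 0.763/n), which is 0.335 for n = 51. With a true value of 0.369 (standard error 0.0676) the test rejects with probability 0.69; with 0.465 (standard error 0.0698), 0.97.

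| Resection rate | Resected-only survival with no effect | False-positive rate |
|---|---|---|
| 51% | 37-46% | 69-97% |
| 65% | 31-36% | 41-75% |
| 88.9% | 25-27% | 11-17% |

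**4. What the primary analysis would need**

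For n = 100 and complete follow-up, the lower confidence bound on the log(−log) scale at one-sided 0.05 is 23.6% when 31% survive and 24.5% when 32% survive, so about 32% is needed. At 2-sided 0.05 it is 23.1% at 32% and 24.0% at 33%, so about 33% is needed.

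**The case against.** The intention is clear elsewhere. The Endpoints section names the primary endpoint and its population, two treatment sections keep early stoppers in, and the sample size section gives the benchmark and a one-arm calculation. This is also a journal article, and the exact one-sample test or interval method may properly sit in a fuller document. That much stands: the missing name of a test is not itself the finding. The populations are different, because the article states them and they conflict with its own endpoint list.

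Four stronger readings are tempting, and the documents do not support them.

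- A reader might infer that the primary endpoint will never be estimated or tested. The text shows only that the one method stated does not deliver it.
- A reader might infer that resected-only survival will be set against 23.7%. No section proposes this, and the endpoint list keeps resected-only survival secondary and per-protocol.
- A reader might infer a log-rank test against the institutional cohort. Nothing says so; next to the Cox predictor analysis, the sentence reads naturally as subgroup comparison.
- A reader might infer that everyone lost before surgery is left out. Progression found at restaging could fit the wording of the PFS group; only those stopping for toxicity or performance status clearly fit neither group.

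The illustration also depends heavily on the resection rate. Quoting only the 51% row would overstate it, since the institution's own series, whose denominator may be selected, gives 88.9%.

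**Conclusion.** The contradiction is real and touches the primary endpoint. As written, the survival-analysis method produces resected-only disease-specific survival, which is a secondary estimand, and PFS in a subset, where the endpoint list asks for both in all enrolled patients. The pairwise log-rank test cannot serve the one-arm hypothesis.

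The size of the possible error is conditional. Only if resected-only survival were read against 23.7% would the false-positive rate be about 11-97%, depending on the resection rate and on the assumed 0-10% survival in unresected patients. It stays above the nominal 5% throughout that range. This should be corrected before analysis, because a statistician who follows the section literally would compute the wrong quantity.

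**What to change.** Rewrite the Survival analysis paragraph to say:

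1. **Primary.** Kaplan-Meier 36-month disease-specific survival in all enrolled patients, with one one-sample test or confidence bound against 23.7% at a single stated alpha. Either state one-sided 0.05, which fits N = 100, or keep 2-sided 0.05 and restate power as about 0.83-0.85. Correct the printed 0.5 in Sample size calculation to match.
2. **PFS** in all enrolled patients.
3. **Resected patients.** Disease-specific and recurrence-free survival as secondary per-protocol results, not compared with 23.7%.
4. **Log-rank tests** for exploratory subgroup comparisons only, not for the primary endpoint.

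The cost is one reworded paragraph and one corrected alpha, submitted as a protocol amendment. No new data or visits are required.

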#### Chemotherapy

Following informed consent, FOLFIRINOX will be administered either in Verona or in local hospital operating within a regional oncologic network on a 14-day cycle for up to 12 cycles (minimum 8). Fluorouracil will be administered as a 400-mg/m2 bolus on day 1, then as a 2400 mg/m2 continuous infusion for 46 h. Leucovorin calcium, 400 mg/m2; oxaliplatin, 85 mg/m2; and irinotecan hydrochloride, 180 mg/m2, will be administered on day 1. Protocol-specified treatment modifications will be undertaken when significant toxic effects occur according to the Common Terminology Criteria for Adverse Events, version 4.0. Treatment discontinuation for severe toxicity or performance status deterioration/disease progression will be recorded. Patients discontinuing chemotherapy will not be considered for SBRT and will be included in the intention-to-treat analysis.

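### Three-year disease-specific survival in the resected subset is counted from diagnosis, so it includes months of treatment during which no member of the subset can die

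*Protocol article*

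**What the plan says.** In the protocol article, the Survival analysis section states that "the disease-specific survival (for patients receiving pancreatectomy) will be calculated from both the date of diagnosis". It then lists last follow-up and recurrence or death from disease. As printed, the sentence offers these as a second item after the word 'both', although they can only be end points of the interval. Diagnosis is the one start date given.

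The Endpoints section lists among the secondary endpoints "3-year disease-specific survival in the subset of patients undergoing resection (per-protocol"). The primary endpoint is separate: "The primary endpoint is the 3-year disease-specific survival (intention-to-treat").

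Membership of the resected subset is settled late. Chemotherapy runs "on a 14-day cycle for up to 12 cycles (minimum 8"). Patients who stop chemotherapy, or who are not eligible for exploration at restaging, leave the protocol pathway and are kept in the intention-to-treat analysis. Candidates for surgery who meet two further conditions receive SBRT: "SBRT will be planned within 4 weeks from chemotherapy completion", with "delivery of 30 Gy in 5 consecutive daily fractions to the PTV". A second restaging follows, then exploration, where distant metastases rule out resection. The article mentions no surgery-date origin, landmark or time-dependent term.

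**The concern.** The subset is defined by an event that happens months after the clock starts. A patient who dies before surgery cannot be in it, so every resected patient is credited with a stretch of guaranteed survival. Read as survival after resection, the 3-year figure is too high. Set beside the intention-to-treat figure, it would look better even if resection did nothing, because the early deaths have been removed from one figure and not from the other. The article plans to report both figures, so readers are likely to make that comparison.

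**Working it through.** **Plan's own figure.** There is none to reproduce. The article gives no expected survival for the resected subset and no time to surgery. The sample size of 100 rests on 23.7% against 37% for the whole cohort, and no resected-subset quantity enters it.

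**Step 1: guaranteed time from the stated schedule.** Inputs are 8 to 12 cycles of 14 days (Chemotherapy section), 0 to 28 days to SBRT planning and 5 daily fractions (SBRT section). One month is taken as 30.4375 days.

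- Shortest: 8 × 14 + 0 + 5 = 117 days = 3.8 months.
- Longest: 12 × 14 + 28 + 5 = 201 days = 6.6 months.

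Two intervals are not stated: diagnosis to first cycle, and end of SBRT to surgery. Taking the first as zero and assuming 2 to 8 weeks for the second gives 117 + 14 = 131 days (4.3 months) up to 201 + 56 = 257 days (8.4 months). I use 5 to 8 months as the working range; it is an assumption, not a figure from the article.

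**Step 2: direction.** Let *t* be the time from diagnosis to surgery. For a resected patient, being alive 36 months after diagnosis means being alive 36 − *t* months after surgery, so

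S_diagnosis(36) = S_surgery(36 − *t*) ≥ S_surgery(36),

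because a survival curve never rises. This needs no model and no particular *t*.

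**Step 3: size.** With a constant hazard after surgery, S_diagnosis(36) = S_surgery(36)^((36 − *t*)/36). For 37% and *t* = 5: 0.37^(31/36) = 0.425. For *t* = 8: 0.37^(28/36) = 0.461. The values 23.7% and 37% are the design's whole-cohort rates, borrowed as illustrations; 50% is added because resected patients may do better.

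| True 3-year survival from surgery | *t* = 3.8 | *t* = 5 | *t* = 6.6 | *t* = 8 |
|---|---|---|---|---|
| 23.7% | 27.6% | 28.9% | 30.9% | 32.6% |
| 37% | 41.1% | 42.5% | 44.4% | 46.1% |
| 50% | 53.8% | 55.1% | 56.8% | 58.3% |

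At 5 to 8 months the gain is 5.5 to 9.1 points for 37%, 5.2 to 8.9 for 23.7%, and 5.1 to 8.3 for 50%.

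**Step 4: what a comparison by resection status would show if one were made.** Suppose all patients have 37% survival at 36 months from diagnosis under a constant hazard, resection has no effect, and 60% (assumed) of those alive at *t* are resected.

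- Survival to *t* = 5 is 0.37^(5/36) = 0.871. Resected: 0.37/0.871 = 42.5%. Not resected: 0.4 × 0.37/(1 − 0.6 × 0.871) = 31.0%.
- Survival to *t* = 8 is 0.37^(8/36) = 0.802. Resected: 0.37/0.802 = 46.1%. Not resected: 0.4 × 0.37/(1 − 0.6 × 0.802) = 28.5%.

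A simulation of 2 million patients gave the same figures. Measured over 36 months from surgery, the resected group returned to 37%.

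**The case against.** The strongest reply is that the sentence is garbled: 'both' may be a slip for 'between', or a second start date may have been lost. That stands as a caution about intent, but either way the sentence needs correcting, and followed as printed it starts the clock at diagnosis. A second reply is that survival from diagnosis among resected patients is a legitimate description. That also stands, provided the figure is labelled as conditional on reaching surgery; the article gives no such label. Third, the size rests on a constant hazard and on intervals that are not stated. That is true, and it touches the size only.

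A reader might infer more than the article supports:

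- *That the plan will show resection to be protective.* The article names no log-rank groups and no Cox covariates, and pairs progression-free survival with unresected patients and disease-specific survival with resected ones. Step 4 applies only if such a comparison is made.
- *That margin status carries the same bias.* Margin status exists only in resected patients, all of whom survived to surgery. With a common time to surgery, changing the origin shifts every time equally and leaves the log-rank and Cox results unchanged; unequal times can alter the ordering, but this is not immortal time between the groups.
- *That recurrence-free survival is lengthened by the same months.* Its origin is not stated explicitly.
- *That the Efficacy assessment section contradicts the analysis.* Following patients for 36 "months postoperatively or from the time of early progression/surgical ineligibility" sets the length of follow-up, not time zero, and more than covers 36 months from diagnosis.
- *That the cited 35.4-month median after resection measures the distortion.* The Background does not say from which date it was counted, and it is overall survival.
- *That the per-protocol label misleads.* The Endpoints section says openly that the set is the resected patients.

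**Conclusion.** The point holds for one named secondary endpoint, 3-year disease-specific survival in the resected subset. As written, it includes at least about 3.8 to 6.6 months of guaranteed survival for a patient who follows the stated schedule through SBRT, plus intervals the article does not state. The upward direction is certain. The size, about 5 to 9 points at 5 to 8 months, depends on the constant hazard and the assumed time to surgery. It would be wrong to conclude that the trial's main result is biased: the primary endpoint is intention-to-treat and not conditioned on resection, and the sample size does not use the subset. The matter should be corrected before analysis, but it does not threaten the design.

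**What to change.** Rewrite the sentence in the Survival analysis section so that disease-specific survival in resected patients runs from the date of surgery to death from disease or last follow-up. State the same origin for recurrence-free survival in that subset, ending at its own event. If a diagnosis-based figure is also wanted, label it as conditional on reaching surgery. If resected and unresected patients are to be compared by log-rank test or Cox regression, use a landmark analysis or enter resection as a time-dependent covariate.

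The cost is a change of wording. Postoperative follow-up is already anchored to surgery, so the date is available and no new data are needed. The resected-subset figures will be less favourable; the primary analysis and the sample size stay as they are.
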